## Discussion

The findings from this study will extend our current knowledge of the effects of evidence-based parenting support delivered through brief, universally offered, low intensity parenting seminars and delivered in school settings. The approach adopted is consistent with the multi-level conceptual model of evidence-based parenting support for educational settings as outlined by Sanders, Healy [58]. The model highlights the unique value of the school setting to help normalize and destigmatize parenting programs and thereby increase parental engagement and widen the reach of parenting programs.

The intervention being tested builds on previous studies showing that a brief three session Triple P seminar series on positive parenting can be effective in changing parenting practices and in improving children’s behavior and adjustment [16, 19, 23]. It extends earlier work by concurrently addressing in the same program, parents’ concerns about their children’s behavior problems, anxiety and peer relationships, particularly school bullying. As the seminar series is a low intensity, brief intervention (Level 2 in the multilevel Triple P system) it is expected that a minority of children and parents with more complex problems may require additional support.

The sample size we intend to recruit will be large enough to examine important moderators of intervention outcomes for both child and parent outcomes including parental completion rates. These moderators include the type of school (state, Catholic, or independent school), the relative social disadvantage of schools, child and parent age and gender, family characteristics (e.g. single parent household), ethnicity, the baseline severity of child social, emotional and behavioral problems, parenting practices and level of program participation such as the number of seminars parents attended. These analyses will help identify the profiles of children and parents who might require early additional support to complete the series and lead to a more nuanced understanding of the reasons for non-completion. As each of the individual seminars are presented as a package and introduced as being relevant to every child, it is likely that some parents would be particularly interested in certain topic and less interested in others. Parents and teachers’ evaluations of the seminars themselves will provide additional end user/consumer feedback to enable the program to adapt and evolve [59, 60].

The interpretation of findings from this study will need to take into account the study’s relative strengths and limitations. Relative strengths include recruiting a large number of schools and parents and the socioeconomic diversity of the schools involved that included state public schools, Catholic Schools and independent schools. The outcome assessments will include reliable, validated and change sensitive assessment tools. The experimental design will enable the program to be sequentially introduced, across the school year, using an incomplete stepped wedge cluster randomised trial design. This variant of the stepped wedge design is particularly useful in evaluating programs in schools. This design involves a systematic replication of intervention effects, with schools servicing as their own controls, rather than relying on randomisation of schools to different conditions e.g., where the intervention is withheld altogether, not available, or only after long delays as in care as usual and waitlist control designs. Traditional RCT’s can be very difficult to implement in regular school settings with differential attrition between intervention and control schools being a particular concern. Another unique feature of the approach will be the inclusion of an intervention component, via a teacher webinar, that will provide guidance to teachers on how to support parents participating in the parenting seminar series. It is widely recognised that improved home-school communication can greatly benefits children’s experience of school, their learning and social and emotional wellbeing, all of which had been adversely affected by COVID-19 [4].

The relative weaknesses of the study include reliance on parents (likely to be disproportionately mothers) as the primary informant for gauging intervention effects. Although parents are the primary target of the intervention and, as such, are crucially important informants about their experience, it is not possible to independently verify parent reported change in their children’s behavior, anxiety or peer relationships. It would have been valuable to plan collection of independent teacher observation data on the child outcomes; however, this is precluded as based on the ethical reasons, teachers were not able to be informed which parents at their school had actually attended the online seminars which were generally scheduled out of school hours.

**Table 1 Tab1:** Incomplete Batched Stepped Wedge Cluster Randomised Trial Design with Project Timeline

Batch	Step	Time (2023)					
		May	Jun/Jul	Aug	Sep/Oct	Nov	Dec/Jan 2024
		Wk0	Wk6	Wk12	Wk18	Wk24	Wk30
1	1	○	●	●			
	2		○	●	●		
2	1		○	●	●		
	2			○	●	●	
3	1			○	●	●	
	2				○	●	●
School Recruitment (N)		100	100	100			
○ Baseline assessment			● Post-intervention assessment			Intervention delivery	

*Note*. Randomisation will determine whether the school will start in step 1 or 2 at each batch

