### Participants and recruitment

The study will involve at least 300 Australian primary schools, from three Australian states, South Australia, Queensland, and Victoria. Following the receipt of relevant ethical clearance, school leaders will be notified about the Thriving Kids and Parents Schools Project through multiple channels (e.g., emails, principal, and parent associations). Priority will be given to government (state-funded) and Catholic schools and if funding permits, independent schools will subsequently be invited to participate. Initial school engagement will utilise an expression of interest (EOI) approach with interested schools being required to complete an EOI form. Following completion of an EOI, further project information will be provided and processes regarding participation negotiated.

Using promotional materials produced by the project team, participating schools will invite their parent body to register online to participate in the TKPSP seminar series. The promotional materials will be specifically targeting schools’ multiple communication channels with the aim of recruiting as many parents as possible. In order to appeal to a wide audience, parents’ eligibility will be determined using the following broad inclusion criteria: (1) presence in the family of at least one child of primary-school age; (2) interested in information about parenting and child development; (3) able to attend online seminars on three separate occasions. Parents will be required to register online and consent to participate will be collected during the registration process.

Utilising the method introduced by Hemming and colleagues [38, 39], assuming an effect size of 0.30 with a type one error rate of 0.001 and an intra-cluster correlation coefficient of 0.05, engaging 50 schools in each batch with an average of more than 10 parents per school will produce sufficient statistical power (> 0.90).

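### Seminar attendance, which is chosen after allocation, is listed as a moderator, and the sample is called adequate for moderators without any interaction calculation

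*Protocol article*

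**What the plan says.** In the Discussion, the protocol article says: "The sample size we intend to recruit will be large enough to examine important moderators of intervention outcomes". It then names about ten moderators. Most are fixed before allocation: school type, school disadvantage, child and parent age and gender, family characteristics, ethnicity, baseline severity and parenting practices. The last item is "level of program participation such as the number of seminars parents attended". The same paragraph counts parents' completion rates among the outcomes and intends the results to help identify families who need extra support.

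The only power statement is under Participants and recruitment. It runs "assuming an effect size of 0.30 with a type one error rate of 0.001" and "an intra-cluster correlation coefficient of 0.05", with "engaging 50 schools in each batch with an average of more than 10 parents per school", which it says "will produce sufficient statistical power (> 0.90"). No interaction size, subgroup share, alpha or power is given for any moderator. That section also says of one level of the school-type moderator: "if funding permits, independent schools will subsequently be invited to participate".

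The Analytic plan sets an intention-to-treat principle for the outcome models and gives no method for attendance.

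**The concern.** **Attendance.** A moderator of a randomised effect has to be defined for every parent independently of allocation, so that treated and not-yet-treated parents can be compared within each of its levels. Attendance does not meet this. Parents choose it once seminars are on offer, and at an untreated assessment it has not yet happened. Those who attend all three seminars are likely to differ from those who attend none in motivation, time and perceived need. A gradient of change across attendance could reflect those differences alone. Placed beside gender or school type, it would be reported as moderation and could inform decisions on whom to support.

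**Adequacy.** An interaction is estimated less precisely than a main effect: for a 50:50 moderator its standard error is twice as large. A calculation for a main effect of 0.30 therefore does not show that the sample suffices for moderators. At stake is how null results are read. A reader told in advance that the sample suffices may take a wide, inconclusive interaction as evidence that the programme works equally for everyone.

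**Working it through.** **Attendance against the design.** In Table 1 each of the six sequences has one baseline assessment followed by two post-intervention assessments. A parent's attendance has no value yet at the baseline, which is the only untreated assessment. The growth model in the Analytic plan estimates change from before to after the intervention. Regressing that change on attendance uses contrasts among treated, self-selected parents, and randomisation of schools does not protect those contrasts.

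**Inputs from the article.** Effect 0.30; alpha 0.001 (two-sided assumed, as the article does not say); ICC 0.05; 50 schools per batch in the power statement; three batches; at least 300 schools intended; more than 10 parents per school (10 used as the floor); 1:1 allocation.

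**Assumed.** Binary moderators, a 50:50 split unless stated, equal school sizes, no dropout.

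**Reproducing the stated power (parallel approximation).**
- Design effect: 1 + (10 − 1) × 0.05 = 1.45.
- Three batches pooled: 150 × 10 = 1,500 parents, 750 per arm. SE = √(2 × 1.45/750) = 0.0622. Power = Φ(0.30/0.0622 − 3.29) = 0.94. The stated figure of more than 0.90 is reproduced.
- One batch alone: 250 per arm, SE = √(2 × 1.45/250) = 0.108, power 0.31. The pooled reading is the one that fits.

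**Interactions at 300 schools × 10 parents (1,500 per arm).**
- Main-effect SE = √(2 × 1.45/1500) = 0.0440.
- Interaction SE = main-effect SE/√(p(1 − p)), where p is the share in one level. School-level, 50:50: 0.0440/0.5 = 0.088.
- A parent-level moderator uses the within-school variance 0.95: √(2 × 0.95/1500)/0.5 = 0.071.
- Detectable interaction with 90% power = SE × (z for alpha + 1.28). The multiplier is 3.29 + 1.28 = 4.57 at alpha 0.001 and 1.96 + 1.28 = 3.24 at alpha 0.05.

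| Moderator | SE | Detectable, alpha 0.001 | Detectable, alpha 0.05 |
|---|---|---|---|
| School-level, 50:50 | 0.088 | 0.40 | 0.29 |
| Parent-level, 50:50 | 0.071 | 0.33 | 0.23 |
| School-level, 20:80 | 0.110 | 0.50 | 0.36 |

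**Power for two illustrative interactions.** Neither size is in the article: 0.15 is half the planned effect and 0.30 is all of it. The splits are 50:50.

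| Interaction | Level | Alpha 0.001 | Alpha 0.05 |
|---|---|---|---|
| 0.15 | School | 0.06 | 0.40 |
| 0.15 | Parent | 0.12 | 0.56 |
| 0.30 | School | 0.55 | 0.93 |
| 0.30 | Parent | 0.82 | 0.99 |

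**Repeated measures.** Generalised least squares on the Table 1 layout, with cluster autocorrelation 0.9 or 1, within-parent correlation 0 to 0.7 and a smaller group of 20% or 50%, gives these ranges at alpha 0.001: 0.03 to 0.64 for an interaction of 0.15, and 0.34 to above 0.99 for one of 0.30. One favourable case (school-level, 50:50, batch-specific periods, cluster autocorrelation 1, within-parent correlation 0.7) has SE 0.052. Its detectable interaction is 0.052 × 4.57 = 0.24 at alpha 0.001 and 0.052 × 3.24 = 0.17 at alpha 0.05.

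**The case against.** **On power.** A reader might infer that the trial is too small for moderators and that the adequacy statement is false. The article does not support that. It attaches "a type one error rate of 0.001" only to the main effect, so testing moderators at that level borrows a threshold. At alpha 0.05 the same formula gives about 93% (school-level) and 99% (parent-level) power for a balanced interaction of 0.30. Most of the listed moderators are measured on parents or children, which is the easier case. The numbers of schools and parents used here are floors, and three assessments per parent can help materially. An interaction of 0.15 is a reviewer's choice. The funding condition on independent schools does not fix their share; the Discussion even describes the participating schools as including them. All of this stands, and it limits the point to an adequacy claim made without a calculation.

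**On attendance.** A reader might also infer that attendance can never be examined causally here. That goes too far. Every school is eventually treated, so the later attendance of start-later parents could be attached to their baseline, and eventual attenders compared across steps in the same week. But the article does not plan this, and it requires that the start date does not change who attends. It does not rescue attendance as an ordinary moderator.

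**On purpose and scope.** Part of the paragraph concerns who completes the series. Predicting completion needs no treatment interaction, so the power figures do not bear on it. Interaction details may also sit in an analysis plan that is not shown. Both objections are fair, but listing attendance as a moderator and asserting adequacy are statements in the article itself.

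**Conclusion.** The attendance point holds without any arithmetic: the article lists a self-selected, post-allocation behaviour as a moderator of intervention outcomes. An analysis that follows the list would present a non-randomised comparison as moderation.

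The adequacy point holds in a limited form. Sufficiency for moderators is asserted, while the only calculation is for a main effect. At the floor sample and a 50:50 split, the detectable school-level interaction at alpha 0.001 (0.40) exceeds the whole planned effect of 0.30; at alpha 0.05 it is slightly below it (0.29). These figures rest on the parallel approximation, ICC 0.05, exactly 10 parents per school, no dropout and a two-sided test. They fall if within-parent correlation is high and rise for uncommon levels, as independent schools might prove to be.

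This concerns secondary analyses described in the Discussion. The primary comparison and its stated power are untouched.

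**What to change.** 1. Restrict the moderator list to variables fixed before allocation. Test each as an intervention-by-baseline-moderator term and report it with a confidence interval.
2. Take attendance off the list. Report it either as an explicitly non-randomised description of change by seminars attended, or as a supportive complier-average effect of any attendance versus none, with the randomised step as instrument. In the second case, say that the exclusion restriction may fail: under Teachers' resources, all participating schools receive teacher materials, which could affect outcomes without parents attending. Say also that one binary instrument cannot identify an effect per seminar.
3. Replace the adequacy statement with the detectable interaction and its assumptions: alpha, level of the moderator, subgroup split, ICC, parents per school and within-parent correlation.

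The cost is a change of wording, at most one supportive analysis, and a less favourable statement about moderators. No extra data are needed.

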**Fig. 1 Fig1:**
[figure not shown]
CONSORT Flow Diagram of Study Procedure

**Table 2 Tab2:** Measures Administration Schedule

Measure name	Item *N*	T1	T2	T3
Demographic Questionnaire		●		
Parenting and Family Adjustment Scale (PAFAS)	30	●	●	●
Parenting Self-regulation Scale (PSRS)	12	●	●	●
Child Adjustment and Parent Efficacy Scale (CAPES)	32	●	●	●
Partner in Education Survey (PIES)	18	●	●	●
Parenting an Anxious Child Scale (PAAC)	12	●	●	●
Brief Spence Children’s Anxiety Scale (BSCAS)	8	●	●	●
Preschool Feelings Checklist (PFC)	20	●	●	●
Parent Satisfaction Questionnaire (PSQ)	10		●	

**Fig. 2 Fig2:**
[figure not shown]
Proposed Multi-level Piecewise Latent Growth Curve Model

## Data Availability

The datasets generated during the TKPSP project will not be made publicly available due to ethical reasons but will be available from the corresponding author on reasonable request. Data sharing is not applicable to this protocol article as no datasets were generated or analysed during the current study.
